### Power calculation

A power analysis for a 2 x 4 mixed factorial design with two groups and four measurement occasions, with α = .05, β = .80, and an effect size of f(V) = .25, resulted in *n* = 179 participants. Taking into account a dropout of 10%, this results in a total of *n* = 199 participants. This power calculation was performed using G*Power 3.1.4 [44].

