***QoL related***			
*Rest-activity rhythm*			
Actometer, worn 24/7 (IS, IV, RA, M10, L5)	X	X	
*QoL*			
DQoL	X	X	
QUALIDEM			X
*Depression*			
Cornell Scale			X

*Note*. MMSE = Mini-Mental State Examination; M10 = Most active period of 10 hours; TUG = Timed Up and Go test; 4MWS = Four Meter Walking Speed test; STS = Sit to Stand test; ADL = Activities of daily living; 8WT = Eight words test; VMS = Visual Memory Span; QoL = Quality of life; IS = Interdaily Stability; IV = Intradaily Variability; RA = Relative Amplitude; L5 = Least active period of five hours; DQoL = Dementia Quality of Life.

^a^Administration pre-baseline used as score at T1.

The complete neuropsychological test battery including the QoL questionnaire has a duration of approximately 90 minutes. For participants with an MMSE score <15, a shortened neuropsychological test battery is administered in order to still be able to detect possible changes in cognitive functioning, without the need for too much effort of the participant (see Table 1). All other outcome measures are the same for all participants. The shortened neuropsychological test battery including the QoL questionnaire has a duration of approximately 40 minutes. All measurements and tests are described in more detail under the heading ‘Materials’.

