##### Statistical analysis

First, to compare the two groups regarding participant characteristics, independent sample *t*-tests or Mann–Whitney *U* tests will be used, depending on the distribution, for age, education level, the number of comorbidities, and the number of medicines used. Chi-squared tests will be performed to compare the groups on gender, subtype of dementia, the use of visual, hearing, or walking aids, the presence of (types of) comorbidities, and the use of (types of) medication. If the two groups differ significantly on a participant characteristic, then this variable can be included as a covariate in the hierarchical mixed model analyses.

Group comparisons will also be made for all the baseline values of the physical, cognitive, and QoL related outcome measures, to ensure equality of the groups at the beginning of the intervention. This will be done by means of an independent sample *t*-test or Mann–Whitney *U* test, depending on the distribution.

Hierarchical mixed model analyses will be used to examine the effect of the intervention on primary (physical), and secondary (cognitive, and QoL related) outcomes. For all physical outcome measures (physical activity, the physical functioning tests, the gait patterns, and ADL) mixed models will be fitted with living room as a level 3 variable, participant as a level 2 variable, and, nested within participants, time of measurement as a level 1 variable. Explanatory variables are time of measurement (four levels with baseline as the reference category) and group (experimental and control condition). A significant interaction effect is indicative of a treatment effect.

All the cognitive outcome measures will be transformed into *z*-scores. Then, a factor analysis will be performed in order to examine whether domains can be formed (e.g., a memory domain). A Cronbach’s alpha of α = .70 will be considered sufficient [69]. Subsequently, both for the possible domains, as for the separate neuropsychological tests (using the raw scores for the latter), mixed models will be fitted. The same levels and explanatory variables apply as for the physical outcome measures. Again, a significant interaction effect is indicative of a treatment effect.

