For the QoL related outcome measures (the parameters of the rest-activity rhythm, the DQoL, QUALIDEM, and Cornell Scale for depression in dementia), also mixed models will be fitted. Again, the same levels and explanatory variables apply as for the physical outcome measures, and a significant interaction effect is indicative of a treatment effect.

The analyses will be performed on an intention-to-treat basis, using the statistical software PC-program SPSS. For all described analyses, a significance level of α = .05 will be used. The appropriate Bonferroni correction will be applied to the significance level in cases of multiple comparisons within a domain.

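### The sample size gives 80% power for a single test at α = .05, so it does not apply to the primary outcomes that will be Bonferroni-corrected, and the family to be corrected is left open

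*Protocol article*

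**What the plan says.** The Power calculation section describes "A power analysis for a 2 x 4 mixed factorial design with two groups and four measurement occasions", run "with α = .05, β = .80, and an effect size of f(V) = .25", which "resulted in *n* = 179 participants". It continues: "Taking into account a dropout of 10%, this results in a total of *n* = 199 participants". The .80 is printed as β, but it functions as the power.

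The Statistical analysis section states: "For all physical outcome measures (physical activity, the physical functioning tests, the gait patterns, and ADL) mixed models will be fitted". The group-by-time interaction in each model is the test of treatment effect. A level of .05 applies to all analyses, with this qualification: "The appropriate Bonferroni correction will be applied to the significance level in cases of multiple comparisons within a domain". No number of comparisons is given. In that section the formation of domains is described only for the cognitive tests, where a factor analysis may produce them.

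The primary outcomes in Table 1 and the Materials section are:
- M10 from the actometer, for physical activity.
- TUG, 4MWS and STS, for physical functioning. The 4MWS yields two outcome measures, mean speed and mean number of steps.
- Katz ADL.
- Sensor gait parameters recorded during the TUG and 4MWS: velocity and step length, with others under examination.

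M10 appears again among the secondary outcomes in Table 1, under rest-activity rhythm: "Actometer, worn 24/7 (IS, IV, RA, M10, L5)".

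**The concern.** The sample size answers the question for one test at the full .05. The analysis runs several primary tests, and some or all of them at a smaller level. Any primary outcome that falls under the correction then has less power than the protocol reports, and a null result on it is weaker evidence than a reader would take it to be.

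The size of the loss and the protection against a false primary claim both depend on which outcomes share a domain. If that grouping is settled after results are known, neither the power nor the error rate of the primary conclusion can be stated.

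**Working it through.** **Inputs.** From Power calculation: α = .05, power .80, f(V) = .25, two groups, four occasions, n = 179, dropout 10%. From Statistical analysis: the test is the group-by-time interaction, and Bonferroni divides α by the number k of comparisons in a domain. The document does not give k, so it is varied here.

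**Reproducing the plan's figure.** For the multivariate repeated-measures interaction in G*Power:
- df1 = (2 − 1)(4 − 1) = 3
- df2 = N − 4 = 175
- λ = N × f(V)² = 179 × .0625 = 11.19

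The noncentral F distribution gives power .8015 at N = 179 and .7990 at N = 178. So 179 is the smallest sample reaching .80. Dropout: 179 / .90 = 198.9, rounded up to 199. Both stated figures reproduce at an undivided α = .05, which shows that no multiplicity allowance is in them.

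**Power at the corrected level.** Same formula, α = .05/k, power for one given outcome, no allowance for clustering by living room:

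| k | Outcomes that would give this k | α | Power, n = 179 | Power, all 199 | N for 80% (with 10% dropout) |
|---|---|---|---|---|---|
| 1 | an outcome alone in its domain | .05 | 80% | 85% | 179 (199) |
| 3 | the three physical functioning tests | .0167 | 66% | 72% | 230 (256) |
| 4 | TUG, 4MWS speed, 4MWS steps, STS | .0125 | 62% | 69% | 243 (270) |
| 6 | those four plus M10 and Katz ADL | .0083 | 57% | 63% | 262 (292) |
| 8 | those six plus two gait parameters | .00625 | 53% | 60% | 274 (305) |

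**Familywise error under two groupings.**
- All physical outcomes in one domain: Bonferroni holds the error at or below .05.
- Physical activity, physical functioning and ADL as three domains, with any one positive counting as support: 1 − .95³ = 14.3% under independence, and at most 3 × .05 = 15% under any dependence.

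**M10.** If physical activity is a domain with one test, M10 is judged at .05. If rest-activity rhythm is a domain with five parameters, the same variable is judged at .05/5 = .01. A p-value between .01 and .05 would then be significant in one place and not in the other.

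**The case against.** The case on the other side has several parts.

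- **Detail left to the analysis plan.** This is a condensed article, and naming families and divisors is commonly done in an analysis plan that is not shown. That stands as far as the missing list goes. It does not remove the conflict between a sample size at undivided α and a stated commitment to divide it.
- **Uncontrolled error.** A reader might infer that the primary claim has no familywise control. The document does not support that. The analysis section handles the physical outcomes together, and if they are one domain the correction controls the whole family. The 14% needs three separate domains and an any-positive rule. The Background words the hypothesis as activity as well as performance; if both were required, error across those two would not be inflated. No decision rule is stated either way.
- **Combining the worst figures.** A reader might put 53% power and 14% error side by side. On the count used here they belong to different readings: k = 8 takes the whole primary set as one family, where error is controlled.
- **Named outcome against any outcome.** The power figures are for one given outcome. If f(V) = .25 held for all four physical functioning outcomes and any one sufficed, power at .05/4 would lie between 62% (complete dependence) and 98% (independence: 1 − .38⁴). This is correct, and it is why the figures must be read per outcome.
- **Two verdicts on M10.** These need both groupings described in the check, and neither is stated. The double listing itself is plain in Table 1.

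**Conclusion.** The stated 80% power does not apply to any primary outcome tested at a Bonferroni-corrected level. For a given outcome the figure is 66% to 53% with 179 participants as k runs from 3 to 8, or 72% to 60% if all 199 contribute. These values assume f(V) = .25 for that outcome and ignore clustering; a positive intracluster correlation would lower them further. An outcome alone in its domain is unaffected.

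Control of the primary hypothesis is undetermined, which is a weaker statement than uncontrolled, because the meaning of a domain is not fixed for the physical outcomes. The listing of M10 as both primary and secondary is a smaller point that opens the possibility of two significance levels for one variable.

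**What to change.** Before analysis:
1. State which physical outcomes form the primary family, and whether the sensor gait parameters belong to it.
2. Apply Holm's step-down procedure across that family in place of Bonferroni. It controls familywise error under any dependence and is never less powerful than Bonferroni on the same family.
3. Test M10 once, as the primary activity outcome, and report it only descriptively under rest-activity rhythm.
4. Restate the power at the corrected level for the chosen family. With six outcomes this is about 57% at .05/6, which is the power at Holm's first step, before clustering.

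A six-outcome family is an example; other definitions would also serve if fixed in advance. The cost is wording, a less favourable power statement, and the possible loss of an uncorrected .05 for M10. Rewording does not restore 80% power: at .05/6 that would take 262 participants, or 292 with 10% dropout.

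### Holm's step-down test could replace single-step Bonferroni within a domain: same family-wise error control, never fewer rejections, and a power gain that runs from nil to about 10 points

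*Protocol article*

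**What the plan says.** The Statistical analysis section of the protocol article gives each outcome its own mixed model and reads the treatment effect from the group-by-time interaction: "A significant interaction effect is indicative of a treatment effect". It sets the level once for everything ("For all described analyses, a significance level of α = .05 will be used") and then adds one sentence on multiplicity: "The appropriate Bonferroni correction will be applied to the significance level in cases of multiple comparisons within a domain". No step-down or other sequential method is named. The number of comparisons in a family is not given, nor is it said which outcomes outside the cognitive battery make up a domain.

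The Power calculation section uses the uncorrected level: "with α = .05, β = .80, and an effect size of f(V) = .25". The .80 printed as β is read here as power.

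**The concern.** Correcting the significance level in the Bonferroni manner means that each of k tests is judged at .05/k, however the other tests turn out. Holm's procedure judges the smallest p-value at .05/k, the next at .05/(k-1), and so on, and stops at the first failure. It starts at the same threshold and only relaxes afterwards. It therefore cannot reject less, and it keeps the family-wise error at .05 whatever the dependence between outcomes.

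The choice could matter here because the hypotheses in the Background are broad. The walking videos are expected to help physical activity, physical functioning and ADL, and also cognition and quality of life. If several outcomes in one family do respond, Bonferroni gives up detections that Holm would keep at the same family-wise error rate.

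**Working it through.** **Inputs.** From the Power calculation section: two groups, four occasions (so the interaction has 3 numerator degrees of freedom), α = .05, power .80, f(V) = .25, 179 evaluable participants, 10% dropout, 199 in total. The family size k and the correlation between outcomes are not in the document. They are assumed and shown as ranges.

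**1. The article's own figure.** Noncentral F with df1 = 3, df2 = N - 4 and λ = f(V)² × N. N = 178 gives power .7990 and N = 179 gives .8015, so 179 is the smallest adequate N. Then 179 / 0.90 = 198.9, rounded up to 199. Both figures reproduce.

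**2. Per-test power under Bonferroni.** The same formula at N = 179 and level .05/k gives 71.3% (k = 2), 65.9% (k = 3), 62.0% (k = 4) and 56.6% (k = 6), against 80.2% uncorrected.

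**3. Hand check of Holm at k = 2.** Use the 3-df chi-square approximation with λ = .0625 × 179 = 11.19. Power is .811 at .05 and .728 at .025, slightly above the exact F values. For two independent outcomes, Holm rejects a given one if its p-value is at most .025, or if it lies between .025 and .05 and the other is at most .025.
- Both affected: .728 + (.811 - .728) × .728 = .788, a gain of about 6 points.
- One affected: .728 + (.811 - .728) × .025 = .730, a gain of about 0.2 points.

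**4. Simulation for larger families.** 50,000 runs per setting, same λ. The figure is average power per truly affected outcome.

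| k | Affected | Bonferroni, independent | Holm, independent | Gain in points at correlation 0 / .3 / .6 |
|---|---|---|---|---|
| 2 | 2 | 72.8% | 78.8% | 6.1 / 5.5 / 5.0 |
| 3 | 3 | 67.6% | 76.5% | 9.0 / 8.2 / 7.2 |
| 4 | 4 | 64.0% | 74.7% | 10.6 / 9.5 / 8.4 |
| 6 | 6 | 58.7% | 70.5% | 11.8 / 10.9 / 9.9 |
| 4 | 2 | 63.9% | 66.4% | 2.5 / 2.4 / 2.2 |
| 4 | 1 | 63.8% | 63.9% | 0.2 / 0.1 / 0.1 |

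Gains were taken before rounding. The chance of at least one rejection is identical by construction, because both methods test the smallest p-value at .05/k. The chance of detecting at least one true effect differed by no more than 0.2 points in any setting.

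**5. Error rates.** With no outcome affected and k = 5, the family-wise error is the same for both methods: .0498 if independent, .0453 at correlation .5. With some outcomes affected, Holm's family-wise error was 3.8 to 4.4%. A lone true null among five independent outcomes is rejected at a rate of .010 under Bonferroni and .028 under Holm, both below .05.

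**6. Sensitivity to clustering.** Living rooms are randomised, but the power calculation carries no cluster term. As an illustration only, halve λ to 5.59. At k = 4 with all affected, power goes from about 29% to about 34%, a gain of about 5 points. At k = 2, power is .487 at .05 and .377 at .025, so two independent affected outcomes give .377 + (.487 - .377) × .377 = .418, a gain of about 4 points.

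**The case against.** The strongest reply is that nothing here is wrong. Bonferroni is a standard, valid correction, the article states it plainly, and choosing Holm swaps one valid method for another. That stands, and it is why this point is optional.

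A reader might infer that the trial forfeits about 10 points of power on its primary outcomes. The document does not support that, for three reasons.
- **Scope.** The correction applies within a domain. Elsewhere in the Statistical analysis section that word refers to cognitive domains that a factor analysis may form. The physical measures are called outcome measures ("For all physical outcome measures (physical activity, the physical functioning tests, the gait patterns, and ADL) mixed models will be fitted"). If domain means only the cognitive ones, the primary outcomes are not corrected and lose nothing.
- **Best case.** About 10 points needs a family of about four or more in which every outcome responds at the full planning effect.
- **Clustering.** The absolute powers ignore it, as the article's own calculation does.

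A reader might also suppose that Bonferroni wastes most when outcomes are closely related. It wastes most when many outcomes are affected. At the planned effect, correlation between them lowers Holm's advantage, as the table shows.

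Nor is Bonferroni without any error-rate merit. It bounds the expected number of false positives more tightly: with one of four outcomes affected and correlation .6, the figure is 0.040 against 0.054 under Holm. It also gives simple simultaneous intervals. The article asks for neither property, so these are small costs and not reasons to keep it.

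**Conclusion.** The point holds as a cheap improvement. Holm's dominance for family-wise error is a mathematical fact and needs no assumption about this trial. Its size does need assumptions: 179 participants, f(V) = .25 for each affected outcome, no clustering, correlations of .3 to .6, and an assumed k. On those terms the gain in per-outcome power is about 5 to 10 points for k = 2 to 4, and about 10 to 11 at k = 6, when all outcomes in the family respond. It is about 2 points when two of four respond and close to nil when one does. The trial's chance of finding at least one effect is essentially the same either way. Whether the primary physical outcomes are touched depends on their being treated as a domain, which the document leaves open.

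**What to change.** Replace the multiplicity sentence with:

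> In cases of multiple comparisons within a domain, the k p-values are ordered and tested by Holm's procedure: the smallest against .05/k, the next against .05/(k-1), and so on, stopping at the first non-significant result.

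This changes one sentence. It leaves the design, sample size, outcomes and models alone, and the ordered p-values can be compared by hand from the software output. It should be settled before unblinded results are seen, so that the switch cannot look data-driven.

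The downsides are small. Simultaneous confidence intervals are less simple than under Bonferroni. Ordinary 95% intervals reported beside the tests may not agree with the Holm decisions, and the report should say so. The bound on the expected number of false positives is looser.

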### Ethical considerations

The Medical Ethical Committee of the VU University Medical Center approved for this study.

## Discussion

The aim of this study is to examine the effect of observing videos of walking people on physical activity, physical functioning, and ADL, as well as on cognitive functioning, the rest-activity rhythm, QoL and depression, in older adults with dementia. This is examined using an RCT design, in which videos are shown in shared living rooms of residential care facilities. Since it is not possible to have participants of both conditions in the same living room (this would require videos of both conditions being shown in one living room, causing participants of each group to see videos of both conditions), living rooms instead of individual participants are randomly assigned to the experimental or control condition.

This study has several strengths. First, the study is highly feasible. For the intervention days, the only actions that are asked of caregivers are turning the televisions on and off, and writing down a minimum amount of information. This also implicates that if this intervention has beneficial effects on one or more of the outcome measures, the intervention is easily applicable in daily life in residential care facilities, and possibly also in home care settings. The applicability is due to the little amount of time needed, that is, only for turning on and off the televisions, and also to the limited associated costs. Another strength of this study is that it gives an extensive insight in the effects of the intervention on (the quality of) daily life functions, such as physical functioning, as well as on QoL itself. Additionally, some outcome measures are measured objectively, through the use of actometers or sensors.

There are also challenges in this study. Actually, one of the advantages of the study is a challenge at the same time. Since the intervention does not require much time and attention from caregivers or researchers, they are not necessarily present in the living room all the time. It is therefore difficult to get a good idea of whether and how long residents are present in the room, and how long they watch the videos. This is overcome as good as possible, without the need for much additional time and effort, by asking caregivers to write down whether participants were present/absent in the living room during an intervention day. In addition, to know whether participants watch the videos being shown, additional observations are made by the researchers by means of behavioral and focal sampling techniques.

Another aspect to take into consideration is the large number of tests that is administrated. Especially the duration of the complete neuropsychological test battery containing the DQoL may be demanding for the participants. Therefore, test administrators are instructed to pay attention to among others fatigue of participants, and, if necessary, look for a good moment for a short break, or even postpone a part of the test administration.

Beneficial effects may obviously manifest themselves through improvements in the outcome measures. However, as partly reasoned elsewhere [52], since many of the measured functions typically decline with age and/or dementia, stabilization or a decreased decline in these functions would also be an important beneficial effect of the intervention. Indifferently how the beneficial effects will manifest themselves, this intervention is expected to be a feasible means for these beneficial effects to occur. In sum, observing videos of walking people is expected to give rise to beneficial effects on physical activity, physical performance, cognition, and QoL related outcome measures, in older adults with dementia.

